**Table 2 Tab2:**
[figure not shown]
Flow diagram of the study

*Abbreviations: UL* ultrasound, *AVF* arteriovenous fistula, *CO* cardiac output, *AF* access flow, blood samples F blood samples for future research, blood samples a: blood samples acute (for sub study 1)

*: When possible for the new AVF, **: At selected sites only, ^: only for new AVFs

### Sample size and statistics

#### Prevalent AVFs

Al-jaishi et al. and Almasri et al. [9, 10] found a primary patency rate and assisted patency rate for AVFs after 1 year to be 60–69%. Lin et al. found a decline in the incidence of interventions from 30 to 12% after 1 year in the FIR group compared to the control group [23]. We wish to detect an improvement in the overall patency rate and therefore a decline from 35 to 10% in the number of prevalent AVFs with at least one intervention or without function after 1 year of treatment. The 10% is chosen since Lin’s study is from 2007 and we suspect an improved vascular surgery, perhaps with a reduced incidence in interventions. With a power of 80% and a significance of 5% we need 43 patients in each group. With an expected drop out of 20%, the number is 52, resulting in a total of 104 patients for the prevalent AVF group.

Because of the inhomogeneous group in the prevalent AVFs, the patients will be stratified according to previous interventions in the data analysis.

#### Incident AVFs

Hemodialysis patients at the largest dialysis centre in Denmark have a mean of 100 days (SD ± 46) from placement of a new AVF to successful cannulation (defined as a successful HD session with two needles in the AVF). Several guidelines suggest cannulation of a new AVF to be 28–56 days after establishment [2, 3]. Therefore, the minimal relevant difference between the intervention and the control group, which we would like to detect is a decrease from 100 to 70 days before successful cannulation. With a power of 80% and a significance of 5% the number of patients needed for inclusion is 37 patients in each group. With an expected drop out of 20%, the overall number Is 81. Due to equal randomization the total number is 82.

Continuous variables will be expressed as mean ± SD when normally distributed and compared by paired and unpaired *t-test* as appropriate. Non-normally distributed variables will be described as median (range) and compared by Wilcoxon signed rank test and Mann-Whitney U test as appropriate. Categorical variables will be described as numbers and percentages and be analysed by Chi-squared test to compare differences between the intervention and control group.

Survival curves of patency will be calculated by the Kaplan-Meier method and compared by the log rank test. A *p*-value < 0.05 is considered significant.

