Studies investigating possible therapies that improves the AVF maturation and survival are scarce. Since the dialysis population is getting older, they present with more comorbidities, and thereby an increased risk of AVF maturation failure. Therefore, there is a need of new interventions that may improve the AVF maturation. FIR is a suggested treatment modality with promising results in the presently available studies [22–24]. There is an urgent need of further studies to explore this treatment. Cannulation of the AVF is by several guidelines suggested to be between 28 to 56 days [2, 3]. However, a huge difference between countries is seen. Early cannulation of the AVF has in studies shown not to reduce the AVF survival [14, 30]. In the largest dialysis center in Zealand, Denmark we found a median time to cannulation of 100 days (SD ± 46) suggesting a poor maturation rate. Lin et al. [22] found a significant improvement in maturation within 1 year (defined in successful cannulation in 8 out of 12 dialysis treatments of a 30 day period) in the FIR treated group compared to the control group (82% vs 60%). The primary endpoint for incident AVFs chosen in our study is therefore time to successful cannulation after AVF placement. Since the FIR treatment is supposed to have a thermal effect increasing blood flow and angiogenesis, we also wish to explore the change of access flow, diameter of the AVF and possible change in cardiac output (perhaps due to the increased access flow in the FIR treatment group). A difference in 1 year patency rate is also examined, since FIR treatment also has shown to decrease the incidence of interventions [22, 23].

After placement of the AVF the patency rates are poor. Al-jaishi et al. and Almasri et al. [9, 10] found a primary patency rate after 1 year of 60–65%. The stenosis in the AVF emerges from an endothelial dysfunction, inflammation and smooth muscle cell proliferation leading to intimal hyperplasia and in the end stenosis [16, 17]. The molecular mechanism that are responsible for the intimal hyperplasia is not well established [16, 28, 31]. Factors, such as Nitric Oxide, Heme-Oxygenase, TNF-alpha and MCP-1 are all factors, that are suggested to be of importance to the AVF maturation and stenosis [16, 31].

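### The incident-AVF total of 82 does not follow from 37 per arm with 20% drop-out; it covers about 10% loss, and at 20% loss power for that comparison is about 74–75%, not 80%

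*Protocol article*

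**What the plan says.** The Protocol article sizes its two patient groups separately under Sample size and statistics.

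**Incident AVFs.** Patients at the reference centre "have a mean of 100 days (SD ± 46) from placement of a new AVF to successful cannulation". The target is "a decrease from 100 to 70 days before successful cannulation". From these inputs: "With a power of 80% and a significance of 5% the number of patients needed for inclusion is 37 patients in each group". The drop-out step follows directly: "With an expected drop out of 20%, the overall number Is 81. Due to equal randomization the total number is 82".

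**Prevalent AVFs.** The requirement is 43 per group, and the same drop-out rate is then applied: "With an expected drop out of 20%, the number is 52, resulting in a total of 104 patients for the prevalent AVF group".

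**Discussion.** The 100-day figure, with the same SD of 46, appears again under a different label: "we found a median time to cannulation of 100 days".

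**The concern.** The base size, the drop-out rate and the final total stand in consecutive sentences and do not agree with each other. Two groups with the same stated drop-out rate also receive visibly different allowances. Each prevalent arm grows from 43 to 52, while the incident total grows only from 74 to 82.

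The incident primary endpoint, time from fistula creation to successful cannulation, rests on this calculation. A reader would take it that 80% power survives a 20% loss. If it does not, a null result in the incident group would be judged against a power claim that the protocol's own figures do not support.

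**Working it through.** **Inputs** (Incident AVFs section, except where noted): difference 100 − 70 = 30 days; SD 46; power 80%; significance 5%; 37 per arm; drop-out 20%; total 81, then 82. Allocation is 1:1 (Study design and participants). The article does not state whether the test is two-sided. Two-sided is used here because it reproduces 37; a one-sided test would need 30.

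**Step 1: reproduce the base size.** By the normal approximation, n per arm = 2 × (1.96 + 0.8416)² × 46² / 30² = 36.9, rounded up to 37. This matches the article. The t-test version gives 37.9, or 38. The total before drop-out is 2 × 37 = 74.

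**Step 2: apply 20% drop-out.**

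| Rule | Calculation | Equal-arm total |
|---|---|---|
| Divide by (1 − drop-out) | 74 / 0.8 = 92.5 | 94 (47 per arm) |
| Multiply by (1 + drop-out) | 74 × 1.2 = 88.8 | 90 (45 per arm) |
| Article | 81 | 82 (41 per arm) |

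The second rule is the one that fits the prevalent group: 43 × 1.2 = 51.6, rounded to 52. So 82 falls short even by the more lenient rule, by 90 − 82 = 8 patients. Starting from 38 per arm would widen the gap.

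**Step 3: find the loss that 82 can absorb.** 1 − 74/82 = 9.8%.

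**Step 4: compute power if 20% are lost without endpoint data.** 82 × 0.8 = 65.6 patients, or 32.8 per arm.
- Standard error of the difference: 46 × √(2/32.8) = 11.36 days.
- Normal approximation: 30/11.36 − 1.96 = 0.68, giving power of 75.2%.
- t-test: 73.9%.
- With whole numbers of 32 or 33 per arm, results run from 72.8% (t-test, 32) to 75.5% (normal, 33).
- Difference detectable with 80% power (normal): 2.8016 × 11.36 = 31.8, about 32 days.

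**Step 5: compute power with no loss.** At 41 per arm it is 83.1% (t-test) or 84.0% (normal).

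**Mean or median.** The sample-size text says that patients "have a mean of 100 days", while the Discussion calls the figure a median and still attaches an SD. The formula in Step 1 uses only the 30-day difference and the SD, so the label on the 100 days does not by itself change n.

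**The case against.** The drop-out arithmetic has no good defence, since no other part of the article repairs it. The case on the other side is about how far the consequence reaches, and most of it stands.

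- **Scope.** A reader might infer that the trial as a whole has about 74% power. The documents do not support that. The prevalent group has its own calculation, and the error concerns the incident comparison only.
- **The figure is conditional.** The 74–75% needs the full 20% to be lost before giving primary-endpoint data. The Study visits section counts losses over 18 months, whereas the endpoint is planned around 70 to 100 days. A patient lost after successful cannulation still has a complete primary outcome. The article does not say when the 20% is expected, so realised power could lie anywhere up to the no-loss value.
- **Choice of formula.** The stated 37 comes from the normal approximation, for which the fall is from 80% to 75.2%. By the t-test, 37 per arm gives 79.0%, falling to 73.9%. Like for like, the loss is about 5 points.
- **Origin of 81.** It is tempting to say that a 10% inflation was used, since 74 × 1.10 = 81.4. But 37 + 37 × 1.2, with 20% added to one arm only, also gives 81.4. The article states neither, so the cause is unknown.
- **Prevalent group.** One might also call the 52 per arm too small. At 52 × 0.8 = 41.6 per arm, power for 35% against 10% is 79.0% by the pooled formula, 81.6% by the unpooled and 81.0% by the arcsine. A one-point shortfall that depends on the formula is immaterial.
- **Mean against median.** The mismatch might be read as a reason to recompute the sample size. It is not, because n changes only if the difference or the SD changes.

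**Conclusion.** The passage is wrong as written. The stated incident total is inconsistent both with its own base size and drop-out rate and with the allowance made for the prevalent group. The consequence is moderate: a drop of about 5 points in power, and a detectable difference about 2 days above the 30 that the article treats as the smallest relevant one. This rests on three assumptions: a two-sided 5% test, an SD of 46 in both arms, and 20% of patients lost without primary-endpoint data. If losses come mostly after cannulation, the shortfall shrinks or disappears, but the sentence still misstates what 82 allows for. The differing label on the 100 days is a separate, minor inconsistency.

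**What to change.** Change the wording in the Incident AVFs section in one of two ways:

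1. Keep 82 patients and 20% drop-out, and state that, if those patients contribute no primary-endpoint data, power is about 74–75% and the difference detectable with 80% power is about 32 days.
2. Keep 82 patients and 80% power, and state that the total allows for only about 10% drop-out. This needs a reason why the rate differs from the 20% kept for the prevalent group.

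The first is the cleaner choice, because it does not alter a planning assumption to fit a number. Also use one label, mean or median, for the 100 days in the Incident AVFs section and the Discussion. The prevalent-group figures can stay, and no new sample-size derivation is required.

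The cost is a few words. Neither option adds patients or changes the design; the first makes one power figure less favourable.

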## Background

Worldwide, the number of patients with end stage kidney disease in need of hemodialysis therapy increases [1]. In order to receive an efficient hemodialysis treatment, the patient needs a well-functioning and stable vascular access. Currently, there are 3 options: an arteriovenous fistula (AVF), an arteriovenous graft (AVG) and a central venous catheter (CVC) [2, 3]. CVCs are associated with an increased risk of stenosis of the central thoracic vessels, thrombosis in a present AVF, local and systemic infections and death [4–7]. In a multivariate analysis performed by Bray et al., patients with a tunneled CVC almost had a 7 fold increased risk of death from septicemia compared with patients with an AVF [4].

AVGs are associated with increased risk of infection, stenosis in the AVG and loss of access [6, 8, 9]. A study by Almasri et al. [9] showed the need of an intervention (defined as both surgical and endovascular) during 2 years of observation to be 60% in the AVG group compared to 45% in the AVF group. Conclusively, the AVF is the preferred vascular access. However, the AVF is not without complications. Following the creation of an AVF there is a 20–50% risk of maturation failure and consequently, the AVF cannot be used [10, 11]. Furthermore, up to 45–67% of the AVFs will develop a stenosis, that needs an intervention within 1 year [9, 10]. During the period with a malfunctioning AVF, the patient may need a CVC as an alternative vascular access which leads to an increased risk of infection, more hospital days and death [6]. The poor AVF maturation and patency is due to many factors. High age, female sex, anatomic location of the AVF (primarily radio-cephalic), small vein diameter, comorbidity, surgeon experience and perhaps arterial stiffness, are all risk factors that influence the AVF survival [10, 12–15].

Studies investigating possible therapies that improves the AVF maturation and AVF survival are scarce as stated in the vascular access guidelines by European Renal Best Practice and European Society for Vascular Surgery [2, 3]. Furthermore, it is not well established, what causes the neo-intimal hyperplasia in the AVF leading to stenosis and loss of the vascular access [16, 17]. This makes it even more difficult to clarify potential treatments.

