### Outcomes

The primary endpoint for the prevalent AVFs is the difference in the overall patency rate between the treatment and control group after 12 months. The overall patency rate is defined as the AVFs without intervention and still in function after 1 year of treatment.

The secondary outcomes are the difference after 12 months in the treatment and control group in: access flow, number of abandoned AVF, change of vascular access to CVC or a new AVF, cardiac output, cannulation pain and number of patients with steal syndrome. Additional secondary outcomes are cardiac output and arterial stiffness at baseline as markers for AVF patency. Finally, the acute changes in the inflammatory and vasodilating factors after one FIR treatment will be compared to changes in the control group.

The primary endpoint for the incident AVFs is the time from placement of an AVF to successful cannulation (defined as a successful hemodialysis treatment with two fistula needles placed in the AVF). The secondary outcomes is the difference between the treatment and control group after 12 months in: number of interventions, diameter of the AVF measured by ultrasound, number of abandoned AVF, number of vascular access change (CVC or new AVF), number of primary patency, change in access flow, change in cardiac output, cannulation pain and number of patients with steal syndrome. Additional secondary outcomes are cardiac output and arterial stiffness at baseline as markers for AVF maturation and patency.

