## Discussion

The present study will examine the effect of FIR treatment on AVF maturation and overall patency rate through a randomized, multicenter, open-labelled trial. Furthermore, the acute effects of FIR in terms of changes in anti-inflammatory and vasodilating factors during FIR treatment will be explored and arterial stiffness as a marker for AVF maturation and patency will also be investigated.

After placement of an AVF there is a high risk of maturation failure and need of assisted patency [9, 10, 14]. Approximately 22 to 37% of created AVFs fails and will never be used. By 1 year, 40% of all AVFs fails or have required at least one intervention [10]. Maturation of the AVF depends on several patient related, but also surgically related factors. Factors such as comorbidity (diabetes mellitus, peripheral vascular disease), female sex, length of ESKD, anatomy of the vessel, surveillance after AVF placement, anatomic placement of the AVF and the surgically procedure itself have all been shown to have an influence on the AVF maturation [12, 13, 15, 28, 29].

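### The incident-AVF primary endpoint is sized as if every fistula had a cannulation time, although the protocol expects 20–50% never to be used and FIR may change that share

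*Protocol article*

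**What the plan says.** The Outcomes section of the protocol article states: "The primary endpoint for the incident AVFs is the time from placement of an AVF to successful cannulation". Success means a dialysis session completed with two needles in the fistula.

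Under Sample size and statistics, Incident AVFs, patients at the largest centre "have a mean of 100 days (SD ± 46) from placement of a new AVF to successful cannulation". The target is "a decrease from 100 to 70 days before successful cannulation", and "With a power of 80% and a significance of 5% the number of patients needed for inclusion is 37 patients in each group". A dropout allowance brings the total to 82, or 41 per arm.

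The same section then gives general rules: t-tests for normally distributed continuous variables, Wilcoxon and Mann-Whitney tests for the others, and chi-squared tests for categorical ones. It adds: "Survival curves of patency will be calculated by the Kaplan-Meier method and compared by the log rank test". It names no test for time to cannulation and gives no rule for a fistula that is never cannulated.

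Three other places bear on this:
- Background: "there is a 20–50% risk of maturation failure and consequently, the AVF cannot be used".
- Discussion: "Approximately 22 to 37% of created AVFs fails and will never be used". It also cites an earlier trial in which 82% of FIR fistulas and 60% of control fistulas matured within 1 year, and uses that result to motivate the endpoint.
- Study visits: a change of vascular access counts as loss to follow-up.

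**The concern.** A fistula that never matures has no time to cannulation, so it has no value to enter into a mean. Read together, the mean-based sample size, the generic tests and the mention of survival methods for patency alone point to a comparison among cannulated fistulas. Such an analysis has two problems.

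- **Fewer data.** The number of usable times falls below the number that the calculation requires. The follow-up rule adds to this, because a patient whose failed fistula is replaced by another access leaves follow-up without a time.
- **Loss of the randomised comparison.** Being cannulated is decided after randomisation, and the article itself cites evidence that FIR changes it. If more FIR fistulas mature, the cannulated groups are no longer comparable. The extra matured fistulas earn FIR no credit in a comparison of days.

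At stake is a primary result that could miss a real benefit on maturation.

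**Working it through.** **1. The stated figure.** Inputs from the Incident AVFs section: difference 30 days, SD 46, power 80%, significance 5% (taken as two-sided).

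n per group = 2 × (46/30)² × (1.960 + 0.842)² = 36.9, so 37. This reproduces the article. The formula compares two means and assumes that every patient supplies a time.

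**2. Power if only cannulated AVFs contribute.** The shares never cannulated come from the Background and Discussion. Two-sample t-test, 30 days, SD 46, 41 per arm, no other dropout:

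| Never cannulated | Times per arm | Power |
|---|---|---|
| 0% | 41 | 83% |
| 20% | 32.8 | 74% |
| 37% | 25.8 | 63% |
| 50% | 20.5 | 53% |

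In total, 82 × 0.8 = 65.6 down to 82 × 0.5 = 41 fistulas would have a time. Keeping 37 cannulated per arm needs 37/0.8 = 47, 37/0.63 = 59 or 37/0.5 = 74 per arm, before dropout.

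**3. If FIR changes the share that matures.** Failure is set at 40% control and 18% FIR, from the cited 60% vs 82%. Per 100 patients, control has 60 cannulated at a mean of 100 days. FIR has 60 at 70 days plus 22 rescued fistulas, meaning those that would have failed without FIR. The documents give no mean time for rescued fistulas, so it is varied as an assumption:

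FIR mean = (60 × 70 + 22 × rescued mean)/82

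Power was simulated with 41 per arm, lognormal times, SD 46, and never-cannulated fistulas ranked last in the all-randomised test:

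| Rescued mean (assumed) | FIR mean | Gap from 100 | t-test, cannulated only | Mann-Whitney, cannulated only | Mann-Whitney, all randomised |
|---|---|---|---|---|---|
| 150 | 91.5 | 8.5 | 9% | 17% | 66% |
| 120 | 83.4 | 16.6 | 27% | 36% | 79% |
| 100 | 78.0 | 22.0 | 41% | 57% | 87% |
| 70 | 70.0 | 30.0 | 69% | 85% | 95% |

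If FIR only raises the share that matures and leaves times unchanged (mean 100 days in both arms), the cannulated-only t-test favours FIR in about 3% of runs. The all-randomised ranked test does so in about 43%.

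**4. The opposite case: FIR speeds maturation (100 to 70 days) and failure is equal in both arms.** Same simulation, with the log-rank test standing in for Gray's test and failures kept at risk to day 365:

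| Failure, both arms | Mann-Whitney, cannulated only | Mann-Whitney, all randomised | Log-rank, all randomised |
|---|---|---|---|
| 20% | 90% | 61% | 25% |
| 30% | 85% | 42% | 16% |
| 40% | 79% | 26% | 10% |

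Simulated figures vary by a few percentage points between runs.

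**The case against.** The article is a condensed account, and an analysis plan may settle this. It names no test for time to cannulation and states no exclusion. Sizing on means does not fix the final test, and the sentence on survival curves does not say that they are used for patency alone. All of this stands. A reader might infer that the plan excludes never-cannulated fistulas, or that they can only be dropped. The documents do not support either reading, because Mann-Whitney is already listed and can take those fistulas as the worst rank.

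A reader might also infer that the result is probably biased against FIR because rescued fistulas mature late. No passage gives their timing. The 9% power belongs to the most unfavourable of four assumed values, and the range runs up to 69%.

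Nor would a maturation benefit necessarily go unseen. Abandoned fistulas, access changes and primary patency are secondary outcomes for incident AVFs. The failure rates are from the literature, and the trial's surgeons are experienced and apply vein-diameter criteria, so the local share may differ.

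Finally, the stated target is speed. If FIR affects speed alone, an all-randomised test has less power than one on cannulated fistulas, and Gray's test would lose the most.

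What remains is what the article does fix: a sample size that needs a time for every fistula, next to its own statement that a fifth to a half will never be used. Secondary outcomes do not repair a primary comparison that is not between the groups as randomised.

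**Conclusion.** The point holds in a conditional form. The sample size for the incident primary endpoint is inconsistent with the protocol's own maturation figures, and the methods as written lead most naturally to an analysis of cannulated fistulas only. That reading is implied, not stated. Under it, t-test power for 30 days at 41 per arm is about 53–74% for 50–20% never cannulated, before any other dropout, and the comparison conditions on an outcome that FIR may alter.

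How much benefit could be missed depends on assumptions. With failure at 40% vs 18%, cannulated-only t-test power is about 9–69% as the assumed mean for rescued fistulas goes from 150 to 70 days, against 66–95% for the all-randomised ranked test. The plan can therefore hide a benefit; the documents do not show that it will. The simulated figures rest on lognormal times, SD 46 in every group and the cited maturation rates.

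**What to change.** In Sample size and statistics, Incident AVFs:

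- State that the primary analysis includes all randomised incident AVFs through 12 months, by Mann-Whitney with never-cannulated fistulas ranked last. Say explicitly that this covers fistulas abandoned or replaced by another access, so that the loss-to-follow-up rule in Study visits does not remove them.
- As support, show cumulative incidence of cannulation by arm, with abandonment, access change, death and transplantation as competing events.
- Report days among cannulated fistulas as description only.
- Restate the power for N = 82 under this analysis, with stated assumptions for the share never cannulated in each arm.

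No new data are needed: the article already has readiness for cannulation assessed at 4 weeks and weekly thereafter. It is more than a wording change, however, because the power statement must be redone. If FIR speeds maturation without changing the share that matures, the ranked test has about 61%, 42% and 26% power at 20%, 30% and 40% failure, against roughly 80–90% for Mann-Whitney on cannulated fistulas. Gray's test as the primary test would cost more in that case (about 25%, 16% and 10% by the log-rank stand-in), which is why the ranked test is preferred.
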